| Trial Objectives | 
General Objectives
The overall objective of this trial is to identify a safe and effective treatment for VL in HIV co-infected patients.
 
Primary Objective:
To evaluate at day 29 assessment the efficacy of a combination regimen of AmBisome® + miltefosine and AmBisome® monotherapy in Ethiopian co-infected HIV + VL patients.
 
Secondary Objectives:
1. To evaluate relapse-free survival at day 390 (after initial cure at day 29 or cure at day 58 after extended treatment).
2. To assess safety of the regimens.
 
Other objectives:
1. To evaluate of viral load and CD4 count in all patients
2. To evaluate the pharmacokinetics of ARV, Ambisome and miltefosine and immune function markers in a subset of patients
      |
| Trial Endpoints  | 
Primary Efficacy Endpoints:
The primary endpoint is initial parasitological cure at day 29 and is defined as absence of parasites in tissue aspirate at day 29.
 
Secondary Endpoint:
Relapse-free survival at 12 months as defined as
 
 
The patient being alive and disease-free from day 29 (if initially cured) or day 58 (for those who received an extended treatment) and remains disease-free until the last follow-up assessment (i.e. day 390).
 
 
Safety
 
 
Assessment of safety during treatment and follow-up based on clinical adverse events, laboratory parameters during treatment and 1 month (after end of initial treatment or end of extended treatment) follow-up.
 
 |

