#### **Safety**

Assessment of safety during treatment and follow-up based on clinical adverse events, laboratory parameters during treatment and 1 month (after end of initial treatment or after end of extended treatment) follow-up.

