| Secondary Prophylaxis                                                       |                     |                    |   |    |                |                                                   |                                                 |                 |                  |                  |
| Start                                                                       |                     |                    |   |    |                | x                                     |                                                 | x   |                  |                  |
| Glucose                                                      |                     |                    |   |    |                |                                                   |                                                 |                 |                  |                  |
| Urea, creatinine +
Liver function
(Bilirubin, AST, ALT)  |                     |                    |   |    |                |                                                   |                                                 |                 |                  |                  |
| Safety monitoring
(SAEs only)                                |                     |                    |   |    |                |                                                   |                                                 |                 |                  |                  |

- 1 Includes weight, height, (screening only) vital signs, VL clinical signs and symptoms.
- 2 Performed only when clinically indicated.
- 3 CD4 count not performed in case of extended treatment is needed.
- 4 Tissue aspirate: This will be a spleen aspirate; if the spleen is not palpable a bone marrow aspirate will be done
- 5 Ideally, the same type of tissue aspirate should be performed at screening and at day 29 assessment (except if not clinically indicated).
- 6 Dashed line arrow refers specifically to patients receiving an extended treatment. Solid-line arrow refers to patients cured at day 29 assessment.
- 7 For patients that are parasite negative at day 29 with CD4 count < 200 cells/mL and with no known contra-indication to Pentamidine. Patients need also to be available for the monthly follow-up visits to receive the secondary prophylaxis.

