- 8 For patients that are parasite negative at day 58 after an extended treatment with CD4 count < 200 cells/mL and with no known contra-indication to Pentamidine. Patients need also to be available for the monthly follow-up visits to receive the secondary prophylaxis.
- 9 At each monthly visit, glucose level will be monitored.
- 10 Clinical chemistry tests will be performed at 6 months and 12 months after the start of the secondary prophylaxis.

| Other analyses performed at Gondar site only on a sub-group of patients * |                                                                 |                 |   |    |     |                                                |     |     |
|---------------------------------------------------------------------------|-----------------------------------------------------------------|-----------------|---|----|-----|------------------------------------------------|-----|-----|
| Protocol activities                                                       | Screening                                                       | Treatment (day) |   |    | Day | Follow-up Period (days post initial treatment) |     |     |
|                                                                           |                                                                 | 1               | 3 | 10 |     | 58                                             | 210 | 390 |
| Cytokines, immunoglobulins                                                | X                                                               |                 |   | X  | X   |                                                | X   | X   |
| Microarray                                                                | X                                                               |                 |   | X  | X   |                                                | X   | X   |
| Electrolytes (K+)                                                         | X                                                               |                 |   | X  | X   |                                                |     |     |
| PK samples MF (DBS)                                                       | Please refer to the detailed schedule section 8.6, page 40 & 41 |                 |   |    |     |                                                |     |     |

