## **Laboratory examinations**

Blood will be analyzed for haemoglobin, WBC, RBC, platelets at screening, on day 3, 10, 29, 58 (for patients with negative parasitology at day 29 - done only if clinically indicated), 86 (extended treatment – done only if clinically indicated), 210 and 390. Urea, creatinine, and liver function (AST, ALT, bilirubin) tests will be performed at screening, on day 3, 10, 29, 58 (for patients with negative parasitology at day 29: done only if clinically indicated). Urea, creatinine and liver function will also be mandatorily be performed at day 210 and 390 assessments, if the patient receives the secondary prophylaxis.

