## **8.7. Adverse event definitions and reporting**

### **8.7.1. Adverse Event definition**

An adverse event will be defined as any untoward medical occurrence (any unfavourable and unintended sign, symptom or disease, including an abnormal laboratory finding) in temporal association with the use of the investigational treatment and may or may not be causally related to it.

Abnormal laboratory results will be reported as adverse events if the abnormality occurs or worsens after institution of the study treatment, and if they require clinical intervention or further investigation, unless they are associated with an already reported clinical event.

All safety events that require reporting to the Ethiopian authority (i.e. NHRERC and FMHACA) will be made according to the national regulations.

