### **8.7.3. Eliciting Adverse Event information**

The investigator is required to report all directly observed adverse events and all adverse events spontaneously reported by the trial subject using concise medical terminology. In addition, each trial subject will be questioned about the occurrence of adverse events on a daily basis during the hospitalization period (day 0-29; or until day 58 in case of extended treatment), and 1 month after the stop of treatment (i.e. day 58 or day 86 in case of extended treatment) with a generic question such as “have you felt different in any way/ had any problems since starting the new treatment/the last assessment?” If the response is “Yes”, the nature of the event, the date and time (where appropriate) of onset, the duration, maximum intensity (see below) and relationship to treatment will be established (see below). Details of any

dosage/schedule modification or any corrective treatment will be recorded on the appropriate pages of the CRF.

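### The safety endpoint includes laboratory values 1 month after treatment, but at that visit the blood tests are drawn only if the clinician sees a reason.

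*Protocol*

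**What the plan says.** The Synopsis (Trial Endpoints, Safety) includes in the safety endpoint "laboratory parameters during treatment and 1 month (after end of initial treatment or end of extended treatment) follow-up". Section 2.2.2 repeats it almost word for word: "laboratory parameters during treatment and 1 month (after end of initial treatment or after end of extended treatment) follow-up". Section 8.7.3 dates the visit: "1 month after the stop of treatment (i.e. day 58 or day 86 in case of extended treatment".

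In the section 5 schedule, full blood count, urea/creatinine and liver function carry footnote 2 in the day 58 column for patients without extended treatment and in the day 86 column for those with it. The footnote reads "Performed only when clinically indicated". Section 8.4 largely agrees, giving the blood count at day "58 (for patients with negative parasitology at day 29 - done only if clinically indicated" and putting the same condition on day 58 chemistry and on the day 86 blood count. It does not list day 86 chemistry.

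Later chemistry depends on pentamidine. Section 8.4 states "Urea, creatinine and liver function will also be mandatorily be performed at day 210 and 390 assessments, if the patient receives the secondary prophylaxis", while schedule footnote 10 states "Clinical chemistry tests will be performed at 6 months and 12 months after the start of the secondary prophylaxis".

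Section 10.7 plans summary statistics for haematological and biochemical parameters at every time point.

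**The concern.** The endpoint names a time point at which the plan does not collect laboratory data from everyone. The 1-month table would describe a group chosen by clinical suspicion. Such a group probably over-represents abnormal values, and because treatment is open-label it may be chosen differently in the two arms.

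Silent toxicity is what this can miss. Section 8.7.1 says "Abnormal laboratory results will be reported as adverse events if the abnormality occurs or worsens after institution of the study treatment" (subject to further conditions), so an abnormality that nobody tests for never becomes an adverse event. The general question put to every patient at day 58 or 86 brings out symptoms, and the clinical assessment brings out signs. Neither shows a rising creatinine or transaminase in a patient who feels well.

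The protocol itself gives reasons to look after day 29:

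- **Tenofovir.** Section 8.6 reports more renal toxicity when amphotericin B is combined with tenofovir and asks for close monitoring of concomitant or later use. Tenofovir is in the standard ART regimen (section 7.7), and patients not yet on ART start it during VL treatment.
- **Pentamidine.** It starts at this same 1-month visit, and section 7.8 lists renal failure as a contraindication. Creatinine is still not mandatory there.

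**Working it through.** The main check sets the passages side by side.

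| Visit | Patients | Blood count and chemistry |
|---|---|---|
| Screening, days 3, 10, 29 | all | routine |
| Day 58 | no extended treatment (their 1-month visit) | conditional (schedule footnote 2) |
| Day 58 | extended treatment (their end of treatment) | routine |
| Day 86 | extended treatment (their 1-month visit) | conditional in the schedule; 8.4 gives the blood count as conditional and omits chemistry |
| Days 210, 390 | all | blood count routine; chemistry only with pentamidine |

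Neither 1-month visit has routine safety bloods. Patients given rescue therapy at day 29 are left unclear at day 58: section 8.4 exempts only patients negative at day 29, whereas the schedule exempts everyone without extended treatment.

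**From last AmBisome infusion to the mandatory day 29 tests** (dose days from section 7.2):
- Monotherapy: 29 − 24 = 5 days.
- Combination: 29 − 11 = 18 days.

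**From the last mandatory chemistry to the next scheduled chemistry** (6 months taken as 183 days):
- Cured at day 29, on pentamidine, by section 8.4: 210 − 29 = 181 days.
- The same patient by footnote 10, pentamidine from day 58: 58 + 183 − 29 = 212 days.
- Extended treatment, on pentamidine, by section 8.4: 210 − 58 = 152 days.
- The same patient by footnote 10, pentamidine from day 86: 86 + 183 − 58 = 211 days.
- No pentamidine: no further chemistry is scheduled.

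For the blood count, which is routine at day 210 in all patients, the gap is 181 days (cured at day 29) or 152 days (extended treatment).

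**Tenofovir exposure seen by the day 29 creatinine in new ART starters.** The Synopsis gives a start at about 2–3 weeks: 29 − 21 = 8 to 29 − 14 = 15 days. Section 7.7 gives 2–4 weeks: 29 − 28 = 1 to 15 days.

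**Illustration of lost precision.** The share that would be tested is not in the protocol, so the numbers below are assumed; 66 per arm is the stated maximum. With no event among n tested, the one-sided 95% upper bound on the event rate is 1 − 0.05^(1/n):

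| Tested (n) | Upper bound |
|---|---|
| 66 | 4.4% |
| 33 | 8.7% |
| 13 | 20.6% |
| 7 | 34.8% |

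The bounds treat those tested as representative, so they show only the loss of numbers and not the selection.

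**The case against.** The endpoint sentence can be parsed differently: laboratory parameters during treatment, plus a 1-month evaluation that need not include bloods. Section 8.7.4 fits this reading, since it mentions only a further safety evaluation at 1 month. Conditional testing also looks deliberate, because it appears in both the schedule and section 8.4. Testing is mandatory through the end of treatment. Every patient is examined at day 58 or 86, so a finding can prompt a test. Blood counts return for all at days 210 and 390. Section 15.3 describes AmBisome as less toxic to the kidney than its parent drug, and the 1–15 day figure applies only to new ART starters. The assumed testing shares have no support in the documents.

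Much of this stands as a limit on the size of the problem. The marrow gap ends at day 210, the tenofovir example covers only some patients, and the zero-event bounds are purely illustrative. The alternative parse is possible but less natural. Even if it is accepted, section 10.7 would still tabulate selected data at day 58 and day 86. None of these points supplies 1-month laboratory data for all patients.

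**Conclusion.** The concern holds. The endpoint calls for laboratory values 1 month after treatment, the schedule makes them conditional at both possible 1-month visits, and the analysis section tabulates them regardless. The result is a clinically selected table that no statistical analysis plan can complete.

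The firm measure of size is the gap in scheduled chemistry: 152 to about 212 days for patients on pentamidine, and no further chemistry for the others. How many patients would be tested at 1 month is unknown. The conclusion rests on the natural reading of the endpoint sentence.

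The consequence is limited to delayed, silent laboratory toxicity. End-of-treatment laboratory safety, the clinical adverse events asked about in all patients, the day 29 primary endpoint and the sequential boundaries are unaffected. This should be corrected, but it does not threaten the trial's main conclusion.

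**What to change.** Preferred change:

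- In the section 5 schedule, remove footnote 2 from the full blood count, urea/creatinine and liver function rows at day 58 (no extended treatment) and day 86 (extended treatment).
- In section 8.4, make these tests mandatory at both visits, add day 86 chemistry, and state that patients given rescue treatment are tested at day 58.

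The cost is one small draw per patient at a visit already planned, at most 2 × 66 = 132 draws, with no added visit. Section 15.2 gives 5 mL for the day 58 draw in extended patients. That draw is at end of treatment, so it is only a guide to volume, and the blood volumes in 15.2 would need updating through an approved amendment (section 13).

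If conditional testing is intended, take the 1-month laboratory component out of the safety endpoint in the Synopsis and section 2.2.2, and limit the laboratory tables in section 10.7 to time points at which all patients are tested. That costs only a text edit, but leaves delayed toxicity unmeasured.

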| 
Statistics
 
Summary of analysis
 | 
Primary Endpoint Analysis: Day 29
 
The study is designed and will be analysed according to group-sequential methods, specifically the triangular test. The triangular test is one way of analysing group sequential trials and uses straight line stopping boundaries. It involves analysing the data as they accumulate, with points being plotted relative to a triangular region and stopping when the upper or lower boundary of the region is crossed (Graph 1). It has the advantage over other methods of analysing group sequential trials, such as the discrete sequential probability ratio test, in that a closed continuation region is used ensuring that the trial stops within a pre-specified maximum sample size.
 
The type I error rate and power of the study were set to 5% and 95%, respectively (<math>\alpha=0.05</math>, <math>\beta=0.05</math>) with parameters <math>p_0=0.75</math> and <math>p_a=0.90</math>. Based on these specifications, the boundaries of the test were calculated for the null hypothesis, <math>H_0: p \leq p_0</math>, and the alternative hypothesis, <math>H_a: p > p_0</math> (see Graph 1). Based on the rationale above, rejecting the null hypothesis, <math>H_0: p \leq p_0</math>, (crossing the upper boundary) means that we can consider the regimen for compassionate use while failing to reject the null hypothesis (crossing the lower boundary) means that we cannot consider the regimen for compassionate use. Data from each arm will be analysed (for the evaluable patient population or per protocol analysis) after every 10 patients reach the primary endpoint of initial cure, where the actual values of Z and V will be calculated and then plotted on the graph. Depending on where the point falls, that arm of the trial will either continue collecting data for another 10 patients or will stop, concluding with a rejection of the null hypothesis (adequate efficacy) or a non-rejection of the null hypothesis (inadequate efficacy). In the final analysis, asymptotic properties will be used to calculate unbiased estimators of the response rate and its 95% confidence interval taking into account the sequential nature of the analyses.
 
Secondary Endpoint Analysis:
 
When the analyses concludes that an arm should be stopped (i.e. a boundary has been crossed), survival at 1 year will also be evaluated. Due to sequential design employed and the different treatment options to be determined by day 29 outcomes (i.e. repeat treatment and/or pentamidine prophylaxis), subsequent analyses (i.e. the secondary endpoint) are likely to be descriptive only. Such descriptive analyses will focus on survival (alive and disease-free) at 12 months post day 29 assessment and relapses between day 29 and 12 months follow-up, by arm and day 29 outcome.
 
Safety Analysis
 
Adverse events (AEs) will be described on treatment and during follow-up. AEs will be coded using MedDRA and tabulated by severity / CTC V4 AE grading. Causality of AEs will also be tabulated. Serious Adverse Events (SAEs) will be described by individual narratives based on the SAE reports provided by the site investigators. Summary statistics will be tabulated for haematological and biochemical parameters as well as for ART efficacy (CD4 count, viral load) at each time point.
 |

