## **2. Study Objectives and Endpoints**

### **2.1 General Objectives**

The overall objective of this trial is to identify a safe and effective treatment for VL in HIV co-infected patients.

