## 10. Data Analysis and Statistical Methods

### 10.1. Sample size determination

The sample size will be determined according to the sequential design for the primary outcome to be measured at day 29.

Since we are using a sequential approach, the sample size is not defined or known in advance. The maximum sample size needed per arm would be 66 patients (132 total patients) and the maximum analyses performed would be 7 (see Graph 1, upper horizontal axis). The actual sample size may be less than this, with its value depending on the value of the proportion cured.

Graph 1: Triangular region for study arms showing the boundaries for analysing the sequential trial using the Triangular Test, with the following parameters ( $p_0 = 0.75$ ,  $p_a = 0.9$ ,  $\alpha = 0.05$ ,  $\beta = 0.05$  and  $n = 10$ ).

[figure not shown]

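### The synopsis labels the 5% type I error as that of the study, but the boundary spends 5% in each arm; the chance of accepting at least one regimen is about 8% if both have a 75% cure rate

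*Protocol*

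**What the plan says.** The Statistics part of the protocol synopsis states: "The type I error rate and power of the study were set to 5% and 95%, respectively", "with parameters p_0=0.75 and p_a=0.90". It then sets a null hypothesis that one cure rate is no higher than 75%, against "the alternative hypothesis, H_a: p > p_0", which is one-sided and concerns a single proportion.

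The rest of that part works arm by arm. It says "Data from each arm will be analysed", and on stopping: "Depending on where the point falls, that arm of the trial will either continue collecting data for another 10 patients or will stop". A regimen that crosses its upper boundary may be considered for compassionate use, and this does not depend on the other arm.

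Section 10.1 and the caption of Graph 1 give one triangular region with alpha and beta of 0.05 for the study arms. The maximum is also per arm: "The maximum sample size needed per arm would be 66 patients (132 total patients"), with at most 7 analyses. Section 2.1 gives the general aim: "The overall objective of this trial is to identify a safe and effective treatment for VL in HIV co-infected patients". The protocol has no sentence that assigns the 5% to each regimen, splits it, orders the two tests, or gives the error rate across both.

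**The concern.** An error rate attributed to the study is naturally read as the risk that the trial wrongly puts a regimen forward. Two regimens are tested, each at 5%, and the general aim in section 2.1 can be read as met by either. If neither is better than 75%, there are two chances of a false acceptance, and the risk for the trial can exceed the stated 5%.

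The data safety monitoring board, an ethics committee or a guideline panel reading the synopsis would then have too favourable a figure for the primary analysis. The power is given in the same sentence with the same label, so it needs the same check.

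**Working it through.** **Inputs.** From the synopsis and section 10.1: p0 = 0.75, pa = 0.90, alpha = beta = 0.05, one-sided, a look after every 10 patients per arm, maximum 66 per arm and 7 looks. Graph 1 is not shown in the text available, so the boundary is rebuilt from these parameters with the standard triangular test on the log-odds scale.

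**Step 1: reproduce the protocol's maximum.**
- theta = ln[(0.90 × 0.25)/(0.75 × 0.10)] = ln 3 = 1.0986
- a = (2/theta) × ln[1/(2 × 0.05)] = 4.192, and c = theta/4 = 0.2747
- Z = successes − 0.75n, and V = 0.1875n
- Correction for looks every 10 patients: 0.583 × √(10 × 0.1875) = 0.798
- Upper line: Z = 4.192 − 0.798 + cV. Lower line: Z = −4.192 + 0.798 + 3cV
- The lines meet at n = (4.192 − 0.798)/(0.2747 × 0.1875) = 65.9

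This rounds up to 66 and needs 7 looks, as stated. With a one-sided 0.025 per arm and 95% power, the same construction gives about 75 to 76 per arm; with 0.025 for both errors it gives about 90 to 91. The stated 66 therefore corresponds to the full one-sided 5% in each arm.

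**Step 2: the rule in whole patients.**

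| Patients in arm | 10 | 20 | 30 | 40 | 50 | 60 | 66 |
|---|---|---|---|---|---|---|---|
| Accept if cures at least | not possible (12) | 20 | 28 | 36 | 44 | 52 | 57 |
| Stop without acceptance if cures at most | 5 | 14 | 23 | 32 | 41 | 50 | 56 |

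**Step 3: error per arm.** Exact binomial recursion through these looks at a true cure rate of 75% gives an acceptance probability of A = 0.0398. With the seventh look at 70 patients it is 0.0406.

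**Step 4: across both arms.** The arms contain different patients and each is tested against a fixed 75%, so the two results are independent. The chance of at least one acceptance is 1 − (1 − A)².
- Nominal alpha: 1 − 0.95² = 9.75%
- Exact, last look at 66: 1 − (1 − 0.0398)² = 7.8%
- Exact, last look at 70: 1 − (1 − 0.0406)² = 7.9%

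**Step 5: away from the worst case** (last look at 66).

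| True cure rate in both arms | Acceptance per arm | At least one acceptance |
|---|---|---|
| 75% | 3.98% | 7.8% |
| 74% | 2.82% | 5.6% |
| 72% | 1.38% | 2.7% |
| 70% | 0.65% | 1.3% |

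If only one regimen is at 75% and the other is effective, the chance of a false acceptance is the single-arm rate, about 4% (5% nominal).

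**Step 6: power.** The same recursion at a true cure rate of 90% gives 89.2% per arm with the last look at 66 and 89.9% with the last look at 70, compared with the stated 95%.

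**The case against.** The strongest reply is that the text already shows the 5% to be a per-arm figure. The hypothesis concerns one proportion, the data are analysed and stopping is decided arm by arm, the graph caption attaches alpha to the region for the study arms, and the maximum is given per arm. Section 3.3 rules out a comparative design and describes the trial as establishing the efficacy of two test treatments. The two regimens have separate patients, separate null hypotheses and separate decisions, with no shared control. Many statisticians would not adjust in that setting. No stated rule says that the trial succeeds if either arm crosses.

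Most of this stands. A careful reader can infer the per-arm meaning, and leaving the two tests unadjusted is a defensible choice. It is also true that the excess over 5% is confined to cure rates at or very near 75%: with both at 72% the stated 5% is met. What does not stand is the label. Arguing that the two regimens are separate questions justifies 5% for each; it does not make 5% the error rate of the study.

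Two stronger readings are tempting. A reader might infer that the trial fails to control its type I error and must split alpha or enrol more patients. The documents do not support that, because each regimen's conclusion keeps its own rate, which the rebuild puts slightly below 5%. A reader might also infer that the risk is up to twice the stated figure whenever neither regimen beats 75%. That holds only with both exactly at 75% and with nominal alpha; the exact ratio there is about 1.6 (7.8/5), and it falls quickly below that point.

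**Conclusion.** The point holds as a minor misstatement. The 5% belongs to each arm, one-sided, and not to the study. In the worst case, with both true cure rates at exactly 75%, the chance of accepting at least one regimen is about 7.8 to 7.9%, or 9.75% if each arm spends its full nominal 5%. The 95% power in the same sentence also needs checking.

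The exact figures assume that the rebuilt boundary is the one in Graph 1, which the match to 66 patients and 7 looks supports. They also assume that V is computed under the null rate and that an arm reaching its last look without crossing the upper line is not accepted. The figure across arms rests on the independence of the two arms. The 9.75% does not depend on the rebuild.

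**What to change.** In the synopsis, reword the sentence so that the type I error rate is 5%, one-sided, for each arm. Add that the chance of accepting at least one regimen when both have a true cure rate of 75% is about 8% (at most 9.75%). Say that each arm's result will be reported as a conclusion about that regimen alone.

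Do not carry the 95% power into the new sentence unchecked. Recalculate it for the boundary and look schedule actually used, and restate it per arm at a true cure rate of 90%; the rebuild suggests about 89 to 90%.

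The boundaries, look schedule and maximum sample size stay as they are. The cost is one reworded sentence and a short recalculation, with no extra patients. The price is that the stated operating characteristics will look less favourable.

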#### **10.9. Interim analysis**

There will be sequential analysis every 20 patients (10 patients in each arm), up to completion of the study. A maximum of 7 analysis will be performed. DSMB will consider if both treatment arms should be continued based on pre-defined criteria set in the sequential analysis. DSMB will also review the available safety data (AEs, SAEs) for both treatment arms.

In order for the findings of this study to be generalizable the population included in this study is heterogeneous (i.e. includes relapse and primary VL patients, patients currently on ART and those that will start ART). In order to address potential concerns regarding the heterogeneity of the population and reduce the likelihood of rejecting a treatment that may be effective in a sub section of the population a test to assess heterogeneity will be performed when a treatment is stopped. This test will be

conducted to verify on the available data if there is a signal of interaction ( $p < 0.10$  = possible interaction) between strata (primary VL or relapse; patients currently on ART or patients initiated on ART during the study) and treatment (magnitude of the treatment effect is dependent upon strata). In absence of signal of interaction ( $p > 0.10$ ) the magnitude of the difference in success rates between treatments should be relatively homogeneous across strata. In presence of significant signal interaction, the treatment effect will have to be adjusted on strata to know whether both therapeutic strategies have the same success rate. Depending on the outcome of this test for heterogeneity, recruitment may be continued into one stratum. This decision will be taken by the sponsor following consultation with the DSMB and other relevant authorities.

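### The stated 95% power holds only under the normal approximation; exact power at a 90% cure rate is about 89%, so the type II error is about double the stated 5%

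*Protocol*

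**What the plan says.** The synopsis (Statistics, primary endpoint) states: "The study is designed and will be analysed according to group-sequential methods, specifically the triangular test". Each arm is tested separately against a fixed cure rate. "The type I error rate and power of the study were set to 5% and 95%, respectively", with parameters "p_0=0.75 and p_a=0.90". Data are examined "after every 10 patients reach the primary endpoint of initial cure", when "the actual values of Z and V will be calculated and then plotted on the graph". For the upper boundary the decision reads "crossing the upper boundary) means that we can consider the regimen for compassionate use"; crossing the lower boundary means that the regimen cannot be so considered.

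Section 10.1 says: "The maximum sample size needed per arm would be 66 patients (132 total patients) and the maximum analyses performed would be 7". Section 10.9 says: "There will be sequential analysis every 20 patients (10 patients in each arm), up to completion of the study". Section 10.6 places the final sequential analysis at 66 patients per arm. Section 3.3 presents sequential designs as preserving the pre-specified type I and type II errors. The protocol text reports no exact binomial operating characteristics and prints no boundary as a count of cures.

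**The concern.** The triangular test gets its boundaries from a large-sample approximation that is accurate when the effect is small. A step from 75% to 90% is a log odds ratio of ln 3, which is not small, and the looks come every 10 patients. The nominal error rates may then differ from those that the 0/1 endpoint actually has.

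The type II error matters because the lower boundary stops an arm during recruitment with a negative conclusion. Section 3.3 says that East Africa has no established standard treatment with proven efficacy of at least 90%, so wrongly setting aside a regimen that cures 90% would be costly. The data safety monitoring board and readers would judge such a stop against the stated 5%.

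**Working it through.** **Inputs from the protocol.** p0 = 0.75, pa = 0.90, alpha = beta = 0.05, one-sided, looks every 10 per arm (synopsis); maximum 66 per arm and 7 analyses (section 10.1).

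**Assumption.** The text names Z and V without formulas. The usual definitions are used, with S the number cured among n: Z = S − 0.75n and V = 0.75 × 0.25 × n = 0.1875n.

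**Step 1: reproduce the protocol's maximum.**
- theta = ln[(0.90 × 0.25)/(0.75 × 0.10)] = ln 3 = 1.0986
- a = (2/theta) × ln(1/(2 × 0.05)) = 4.192
- c = theta/4 = 0.2747
- correction for discrete looks: 0.583 × √1.875 = 0.798
- upper boundary: Z = 3.394 + 0.2747V; lower boundary: Z = −3.394 + 0.824V
- they meet at V = 3.394/0.2747 = 12.36, so n = 12.36/0.1875 = 65.9

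That gives 66 per arm: six groups of 10 and a last group of 6, seven analyses in all. Other versions do not give 66: 81.4 without the correction; 90.4 or 105.9 at alpha 0.025, with or without it; 132.2 on the risk-difference scale.

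**Step 2: confirm the nominal rates.** Simulating these boundaries with Z normal, mean theta × V and variance V, gives a type I error of 5.0% and power of 95.0%. So these are the intended boundaries and 95% is their asymptotic value.

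**Step 3: convert to counts and compute exactly.** The probabilities below come from a binomial recursion at a true cure rate of 0.90.

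| n | Inadequate if cured | Adequate if cured | P(stop, inadequate) | P(stop, adequate) |
|---|---|---|---|---|
| 10 | ≤5 | not possible | 0.0016 | 0 |
| 20 | ≤14 | 20 | 0.0101 | 0.1216 |
| 30 | ≤23 | ≥28 | 0.0175 | 0.2983 |
| 40 | ≤32 | ≥36 | 0.0214 | 0.2299 |
| 50 | ≤41 | ≥44 | 0.0221 | 0.1445 |
| 60 | ≤50 | ≥52 | 0.0185 | 0.0794 |
| 66 | ≤56 | ≥57 | 0.0164 | 0.0186 |
| Total | | | 0.108 | 0.892 |

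The false-negative probability has already reached 5% by the look at 40 (0.0016 + 0.0101 + 0.0175 + 0.0214 = 0.0506). No choice of rule at the last look can restore 95%.

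| Last look | Type I error at 0.75 | Power at 0.90 | Cure rate giving 95% power |
|---|---|---|---|
| 66 | 3.98% | 89.2% | 91.4% |
| 70 (cut-off 60/70) | 4.06% | 90.0% | 91.3% |

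Simulation of binomial data agrees to within about 0.1 percentage point. Counting equality as a crossing or not, or deciding the last look by the upper, lower or middle line, leaves the cut-offs unchanged. Without the discrete-look correction power would be 88.6%, but that version does not reproduce 66.

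**Step 4: why the approximation fails.** At pa it takes the drift of Z to be theta × 0.1875 = 0.206 per patient. The true drift is 0.90 − 0.75 = 0.15. The variance per patient is also smaller than assumed (0.09 against 0.1875), but that does not make up for the lost drift.

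**Both arms together.** If both regimens truly cured 90% and the arms are independent, the chance of wrongly rejecting at least one is 1 − 0.892² = 20%, against 1 − 0.95² = 10% as stated.

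**The case against.** The best defence is that 95% is a nominal design value, correctly obtained from the named method. The synopsis says that the rates were set and the boundaries derived from them, and step 2 confirms this. Exact operating characteristics could also appear in a statistical analysis plan that is not at hand. This shows that the method was not misapplied. It does not rescue the statement: the 95% is given without qualification, section 3.3 says that the error rates are maintained, and boundaries already fixed in the protocol have the power they have whatever a later document says.

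The boundaries here are a reconstruction, since neither Graph 1 nor the formulas for Z and V are available. That is a real limit, though agreement on both 66 patients and seven looks supports it.

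A reader might infer more in three ways, none of which the protocol supports:
- **That 66 per arm (132 in total) is an error, because seven looks of 10 make 70.** Section 10.6 places the final sequential analysis at 66 per arm, which is six groups of 10 and a last group of 6. Only the wording of section 10.9 leaves out the shorter last group.
- **That a positive result is undermined.** Type I error is about 4%, below the stated 5%.
- **That the stated error rates are all that supports acting on a lower-boundary crossing.** Section 10.9 has the monitoring board consider continuation and requires a heterogeneity test when a treatment is stopped, with possible further recruitment in one stratum. The plan also calls for point and interval estimates in each arm. These safeguards soften the consequence but do not change the power.

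**Conclusion.** The concern holds as a misstated operating characteristic. Exact power at a 90% cure rate is about 89% with the last look at 66 per arm (about 90% at 70), against 95% stated. That is a shortfall of 5 to 6 percentage points and a type II error of 10 to 11% instead of 5%. The design remains reasonably powered and conservative on type I error; what is wrong is how much confidence a negative result is said to carry. The conclusion rests on the standard definitions of Z and V, the log-odds scale and the usual correction for discrete looks, which together reproduce the protocol's own maximum and number of analyses. Nothing here shows that the planned final estimator is biased, so no change to it is called for on this ground.

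**What to change.** In the synopsis and section 10.1:
- Restate the exact operating characteristics: type I error about 4%, power about 89% at a 90% cure rate with the last look at 66 per arm, and 95% power at a cure rate of about 91.4%. If 95% is kept, label it as the asymptotic design value beside the exact figure.
- Print the boundaries as counts, after checking them against Graph 1. Inadequate: ≤5/10, ≤14/20, ≤23/30, ≤32/40, ≤41/50, ≤50/60, ≤56/66. Adequate: 20/20, ≥28/30, ≥36/40, ≥44/50, ≥52/60, ≥57/66.

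In section 10.9, say that the seventh analysis follows a last group of 6 per arm, so that it agrees with the final look at 66 in section 10.6.

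The cost is a short recalculation, some wording and a less favourable stated power. No extra patients are needed, and the boundaries and looks stay as designed.
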